## 6. Hypothesis Testing

### *a. Primary Outcome*

The primary aim of the study is to test whether modulation of the gut microbiome using a prebiotic food supplement, in addition to protein supplementation, can improve muscle strength versus protein supplementation alone. Thus, the primary efficacy outcome is a variable which measures muscle strength: chair rise time, the time it takes to rise from a standard chair five times, without using one's arms. This was chosen based on the EWGSOP2 guidance for measuring muscle strength in the context of sarcopenia research.

**Primary outcome:** change in chair rise time, operationalised by using chair rise time measured at end of study, and including baseline chair rise time in the statistical model

**Null Hypothesis:** there is no difference in the change in chair rise time between study arm 1 (prebiotic + protein) and study arm 2 (placebo + protein)

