### ***3.2 Supplementary Table S2: Details of adverse events experienced by participants in the PROMOTe trial.***

| No. | Adverse Event                          | Arm | Related to Study? |
|------------|-----------------------------------------------|------------|--------------------------|
| 1          | Bloated, loss of appetite, waist feels bigger | 2          | probably                 |
| 2          | Bloating                                      | 1          | probably                 |
| 3          | Bloating                                      | 1          | probably                 |
| 4          | Flatulence*                                   | 1          | probably                 |
| 5          | Wind                                          | 1          | probably                 |
| 6          | Constipation                                  | 1          | possibly                 |
| 7          | Diverticulitis                                | 1          | possibly                 |
| 8          | Cramps in legs                                | 1          | remote                   |
| 9          | Headaches                                     | 2          | remote                   |
| 10         | Hair loss*                                    | 1          | remote                   |
| 11         | Nose bleeds                                   | 1          | remote                   |

\*Experienced by same participant. Arm 1 = prebiotic. Arm 2 = placebo.

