the protein supplement plus prebiotic food supplement intake arm. After randomisation the supplements will be posted to the participant. Researchers and participants will be blinded as to which group each participant is in. The Kings Clinical Trials Unit will liaise directly with the company providing the supplements to ensure complete blinding of research team. A designated member of the departmental administration team will have access to the unblinded information.

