The International Conference on Harmonisation of Technical Requirements for Registration of Pharmaceuticals for Human Use (ICH) recommends that data from clinical trials be analysed according to a pre-specified statistical analysis plan (SAP) . This SAP has been developed and finalised without knowledge of study arm allocation or study results and all analysis will be carried out blinded.

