### ***Randomisation/Allocation Concealment/Blinding Procedures***

Participants will undergo computer generated block randomisation in twin pairs by the King's College London Clinical Trials Unit (KCTU). They will be randomised as twin pairs, with one twin in each arm. Researchers and participants will be blinded as to which arm each participant is in.

On completion of the data collection, the KCTU will issue a blinded list denoting what arm each participant is in (Arm 1; Arm 2), but without revealing which arm is the intervention and which the placebo, in order to facilitate blinded analysis to be carried out. Full unblinding will not take place until data analysis is complete. Until that point, only the KCTU will have access to the unblinded information.

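### The SAP's null hypothesis attaches treatments to the same arm numbers that are meant to blind the analysts, so the plan as written does not secure blinded analysis

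*Combined protocol and SAP*

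**What the plan says.** SAP section numbers follow its table of contents.

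- **SAP 2.1 (Background and Rationale)** says the SAP was finalised without knowledge of allocation, and that "all analysis will be carried out blinded".
- **SAP 3.2 (Randomisation/Allocation Concealment/Blinding Procedures)** has the trials unit (KCTU) issue, once data collection is complete, a "blinded list denoting what arm each participant is in (Arm 1; Arm 2), but without revealing which arm is the intervention". It adds that "Full unblinding will not take place until data analysis is complete", and that until then the KCTU alone holds the unblinded information.
- **SAP 6.1 (Primary Outcome)** states the null hypothesis as no difference in change "between study arm 1 (prebiotic + protein) and study arm 2 (placebo + protein".
- **SAP 6.2 (Secondary Outcomes)** uses the same arm numbers without naming treatments.
- **SAP 7.2.1 (Primary Outcome, analysis)** describes the primary comparison as arm 1 against arm 2 and labels it blinded.
- **SAP 7.5.2 (Missing baseline covariate data)** requires imputation decisions to be taken before unblinding.
- **Protocol 10.1 (Study Design), Stage 1** says: "A designated member of the departmental administration team will have access to the unblinded information".
- **Supplementary Table S2**, a results table, carries the footnote "Arm 1 = prebiotic. Arm 2 = placebo".

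**The concern.** A two-label code masks treatment only while the people who hold the coded list lack the key. Here the list is described in one section of the SAP, and a treatment is attached to each label in another section of the same document. An analyst who takes both at face value needs no further information to identify the prebiotic arm.

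What is at stake is the period between receipt of the list and full unblinding, when the analysis is done. Several decisions are left to that period, and the SAP presents blinding as their safeguard. If the labels are transparent, that safeguard may be absent while the SAP still describes the analysis as blinded.

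**Working it through.** No arithmetic underlies the main point. It is a cross-check of labels.

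**1. The labels and the key**

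| Place | Label | Treatment attached? |
|---|---|---|
| SAP 3.2, list sent to analysts | Arm 1 / Arm 2 | No, deliberately withheld |
| SAP 6.1, null hypothesis | arm 1 / arm 2 | Yes: prebiotic + protein / placebo + protein |
| SAP 6.2, secondary hypotheses | arm 1 / arm 2 | No |
| SAP 7.2.1, primary model | arm 1 / arm 2 | No, and marked blinded |
| Supplementary Table S2 | Arm 1 / Arm 2 | Yes, same direction as 6.1 |

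One pair of labels runs through the list, the hypotheses and the primary model, and 6.1 gives its meaning.

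**2. Is the list's code separated from that key?** No text in the protocol or SAP says that the numbering in 6.1 is notional, that the KCTU draws its labels independently, or that another code is used. The plan therefore leaves two possibilities open. If the list shares the 6.1 numbering, the active arm is known on receipt. If it is numbered independently, the analysis is masked, but 6.1 then carries arm numbers that may point the wrong way for a reader of the results. The wording needs correcting in both cases.

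**3. How much does Table S2 add?** Under a shared code, a match between Table S2 and 6.1 has probability 1. Under independent, evenly drawn labels (an assumption) it has probability 1/2. The ratio is 1 ÷ 1/2 = 2. If the results were relabelled after unblinding to follow the SAP, a match is certain either way and the ratio is 1. The agreement is thus worth a factor between 1 and 2: consistent with a shared code, and weak as evidence for one.

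**4. Which blinding is exposed?** SAP 3.2 releases the list only when data collection is complete. The labels cannot have influenced participants' behaviour or the measurement of chair rise time. Only analyst blinding is in question.

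**5. What is decided in the exposed period?**
- *Covariates in the primary model.* SAP 7.2.1 adds a baseline characteristic if the arms differ on it, but does not define a difference. The baseline tests in 7.2 may be the intended trigger; the SAP does not say so.
- *Imputation of missing baseline covariates.* SAP 7.5.2 offers mean imputation or an earlier cohort value, with a time window that varies by variable, to be settled before unblinding. This is the one choice that the SAP itself ties to the blind.
- Outlier handling (7.1), adjustment for extra intervention days (5.1) and the microbiome responder definition (5.3) are also open, with less bearing on the primary result or with partial constraints.

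**6. Who holds the key?** SAP 3.2 says the KCTU only. Protocol 10.1 adds a departmental administrator. Both cannot be right.

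**The case against.** The strongest reply is that the brackets in 6.1 simply state which treatments are compared. The SAP was finalised without knowledge of allocation, the list was to be issued later without identifying the active arm, and 6.2 and 7.2.1 use the numbers without treatments. On that reading the KCTU would have numbered its list without regard to 6.1. This is possible, and it defeats any claim that blinding was in fact lost. It does not remove the gap. A key written before allocation is known reveals nothing at that time, but it decodes the list when the list arrives, unless the codes are kept independent, and the plan does not say that they are.

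It can also be said that several of the open choices are constrained: results with and without outliers are to be compared where necessary, 7.2 calls the primary analyses unadjusted, and the subgroups are acknowledged to be unpowered. That stands, and it narrows the consequences chiefly to covariates for imbalance and imputation. It is also true that any two-label list shows whether a choice widens the difference between arms, so recoding alone does not make up for loose pre-specification.

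A reader might infer from Protocol 12.1 that the person holding the code dealt with participants, since the administrative team approaches and enrols them. The documents do not support this. Protocol 10.1 names one designated member without giving that person's other duties. Approach, consent and enrolment come before randomisation, which follows the baseline visit. Nothing shows contact by that person after allocation.

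**Conclusion.** The point holds as a defect in the plan. The SAP commits to blinded analysis on labels that it also defines, and does not state that the trials unit's code is independent of that definition. Analyst blinding is therefore not secured as written. The contradiction over who holds the unblinded information is a second, separate defect.

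A reader might go further and infer that the analysts were unblinded, that Table S2 proves it, or that choices were steered toward the prebiotic. The documents support none of these. No text gives the numbering actually used on the list, Table S2 reports treatments already identified, and no steered decision is shown. There is no numerical bias to report.

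Confidence is high that the wording conflicts, and no more than moderate that blinding was affected in practice. The conclusion assumes that the analysts had access to the SAP, and that the figures not reproduced in the available text contain no statement on coding.

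**What to change.** 1. In SAP 6.1, name the two arms by treatment only (prebiotic + protein; placebo + protein) and remove the arm numbers. Use the coded labels only where the analysis itself is described.
2. Have the KCTU issue neutral codes, assigned at random and unrelated to any trial document. Withhold the key at least until the blind-review decisions (covariates for imbalance, imputation, outliers) and the analysis code are signed off and dated. The sign-off matters as much as the codes, because a neutral label alone does not show when a choice was made.
3. State whether any list already issued used the numbering in 6.1. If it did, say so when the analysis is described as blinded.
4. Reconcile Protocol 10.1, Stage 1 with SAP 3.2 on who holds the unblinded information. If someone in the department does hold it, record that this person takes no part in data cleaning or analysis.

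The cost is SAP wording and one recoded list. Neither the design nor the sample size changes.

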### *b. Secondary Outcomes*

Secondary outcomes include:

- Grip strength
- Short physical performance battery (SPPB) score
- IPAQ - physical activity questionnaire – either overall score or MET minutes/week
- Appetite - SNAQ questionnaire
- Cognition (as measured by CANTAB battery)
- Gut microbiome measures
- Serum metabolites

**Null Hypotheses:** there is no differences in the change of each of the above measures between study arm 1 and study arm 2. [See Section 7.2.2 for further detail on analysis plan].

### **i. Cognition: Factor Analysis**

Key variables will be chosen from the results of each of the tests of the CANTAB cognitive battery. A factor analysis will be carried out using the chosen variables. The same factor

loadings used for the baseline cognitive test results, will be applied to the end of study test results, leaving a baseline factor score and a study-end factor score. These factor scores will be used in the analyses laid out in Section 7.2.1.

### ***c. Safety Outcomes***

All safety outcomes will be reviewed, collated, and reported where relevant. These include adverse events, serious adverse events (SAEs), hospitalisations or other significant medical events.

Adverse effects will be defined as present or absent (coded 1 and 0 respectively) for each participant. Participants who dropped out prior to receiving any of the intervention will be excluded. Each binary safety outcome will be analysed by treatment group using a chi-square test or Fisher exact test. The likelihood of an SAE being associated with the study intervention will be rated as none, unlikely, possible, or probable. Frequencies and percentages of any adverse events in each study arm will be calculated.

## **7. Statistical Analysis**

### ***a. Descriptive Statistics***

All outcomes will be presented using descriptive statistics; normally distributed data by the mean and standard deviation (SD) and skewed distributions by the median and interquartile range (IQR). Binary and categorical variables will be presented using counts and percentages. P values of  $\leq 0.05$  will be considered sufficient to reject the null hypothesis.

Outliers will be assessed by examining plots and checked for possible erroneous entry. Where necessary, results with and without outliers will be compared to assess for discrepancies in the results, and this will be discussed if found to be discrepant.

#### ***i. Food diary data***

The food diary data will be presented in tables, by sex. Paired tests will be carried out to assess for differences between baseline and study end point, two sample t-tests for continuous variables (normally distributed), and Mann-Whitney test for non-normally distributed continuous variables.

Over and under reporting will be assessed using the Goldberg energy intake to BMR (basal metabolic rate) ratio method . BMR will be calculated using the revised Harris-Benedict equation , and multiplied by an adjustment factor for physical activity . A ratio of this adjusted BMR to energy intake (kcal/day) will be generated. Over and under reporters will be identified as those who are two standard deviations above or below this ratio. If over an/or under reporters are identified, an additional dietary table will be presented, with these participants excluded.

### ***b. Main Analyses***

Paired tests will be carried out to assess for differences between each arm at baseline; two sample t-tests for continuous variables (normally distributed), Mann-Whitney test for non-normally distributed continuous variables, and Pearson's chi-squared tests for categorical variables.

All primary statistical analyses will be unadjusted. Subsequent analyses carried out will be adjusted for relevant covariates which are known or suspected *a priori* to be associated with the outcome, as described henceforth. Stata and RStudio will be used for all statistical analysis.

### **i. Primary Outcome**

The primary analysis will compare intervention groups (arm 1 vs arm 2; blinded) on their change in chair rise time at 12 weeks using a linear mixed model. Chair rise time at 12 weeks will be the dependent variable. Twin clustering will be considered as random effects, treatment group as fixed effect. Baseline value of chair rise time will be included as a covariate [See: ]. If, despite randomisation, there is a difference between the two arms for a specific baseline characteristic, for example age, then age will be included as a covariate in the linear mixed models. The estimated difference in mean change from baseline to 12 weeks and the corresponding 95 % confidence interval (CI) will be presented.

The nature of the design of this study, with randomisation by twin pair and therefore clustering within the data will be taken into consideration by using both twin pair identifier (fid) and zygosity as random effects.

The number of participants who experience a 20% reduction in their chair rise time, as has been deemed clinically significant in previous studies (See Section 3.3), will be presented. We acknowledge that none of these studies used an intervention targeting the gut microbiota, however none such studies were available, making these the closest benchmark available.

### **ii. Secondary Outcomes**

Secondary analyses will include linear mixed effects regression models to investigate associations between the change in each of the below variables, adjusting for covariates where relevant.

- Grip strength
- Short physical performance battery (SPPB) score
- IPAQ - physical activity questionnaire – either overall score or MET minutes/week
- Appetite - SNAQ questionnaire
- Cognition (as measured by CANTAB battery)
- Gut microbiome measures – function and composition (from faecal samples) [See Section 7.2.2.1 for further detail].
- Serum metabolites

The change in grip strength, SPPB score, IPAQ score, FI, cognition, and SNAQ will be analysed using the same method as for the primary outcome, including usage of the baseline value for the actual factor as a covariate.

An exploratory analysis will be carried out to assess for any differences in serum metabolite profile between the two arms of the study. Linear mixed models will be used as described in Section 7.2.1 using the metabolite at study end as the dependent variable and including the baseline level as a covariate. Analyses will be adjusted for multiple testing to control the overall type 1 error rate.

## **1. Gut Microbiome Function and Composition**

Stool samples will be collected from all participants at the beginning and end of the study, via post. The DNA extraction will be carried out in our own laboratory, and then the extracted DNA samples will be sent to an external microbiome sequencing and bioinformatic company, who will carry out high-resolution shotgun metagenomics microbiome analysis of all samples. This includes full profiling of microbiota present (composition), functional species group association analysis, as well as measures of alpha and beta diversity for each individual sample.

Once the above information is available, statistical analysis will assess microbiota differences between the two study arms and between twin pairs. Microbiome composition will be analysed with respect to (1) species diversity, (2) compositional differences, (3) functional differences and (4) differences in abundance of taxa. All analysis will take a hierarchical approach; crude models assessing just the variable of interest (prebiotic supplementation), and models adjusted for key biological (age, sex, exercise etc.) and technical covariates (e.g., differences in library size) will be applied.

Differences in species diversity and richness will be compared between each study arm in regression analysis in crude and adjusted models. Distance matrixes characterise the inter-individual differences in microbiota composition; ordination analyses and permutational multivariate analysis of variance (PERMANOVA) will be used to understand differences in composition between each study arm.

ASVs will be collapsed to family, order, and phylum levels, with hierarchical models, adjusted for each potential mediator individually, then fully adjusted. All models will be adjusted for multiple testing.

All twins within each study arm will be used in paired and unpaired tests to assess if microbiota dissimilarity increased with differences in muscle strength, taking relevant covariates (including diet [HEI], BMI and frailty index) into consideration.

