Pairwise comparisons of microbiota (dis)similarity were compared using the Mann-Whitney U test and verified by comparing the Mann-Whitney U test statistic obtained when analysing data with the original group labels to the test statistic distribution obtained by 1,000 group label permutations. The latter comparison was also performed using the Mann-Whitney U test.

Unless otherwise stated, permutational multivariate analysis of variance (PERMANOVA) tests were performed using the `adonis2` function from the `vegan` R package with 1000 permutations and `by = "margin"`, thus assessing the marginal effects of the terms (i.e. each marginal term analysed in a model with all other variables). Multivariate homogeneity of group dispersions was tested using the `betadisper` and `permutest` functions from the `vegan` R package with 1000 permutations and `type = "spatial median"`, which is an implementation of the PERMDISP2 procedure from^12. Distance-based redundancy analysis (dbRDA) tests were performed using the `capscale` function from the `vegan` R package with 1000 permutations and `"sqrt = T"` to prevent negative eigenvalues. With 1000 permutations, the lowest possible P value is  $1/1001 = 0.000999$ .

When performing statistical testing on multiple hypotheses, we used the Benjamini–Hochberg (BH) method to control the false discovery rate (FDR) at a level of 10%. Thus, of all the “statistically significant” associations we report in this context, we expect 10 % of these to be false associations (arising due to chance). When we report the “FDR-adjusted P value”, this is not a P value per se, but rather indicates the FDR at which a given hypothesis would be called significant using the BH method. FDR control was applied to each tested contrast individually, i.e., it accounts for multiple species being tested but does not account for multiple contrasts and across multiple analysed

visits. When we refer to a “nominal” P value, this indicates that the P value is not subjected to FDR control nor otherwise adjusted for multiple hypotheses.

Broad-sense heritability was determined with ACE model (from R package mets). The model estimates how much the phenotype variation stems from additive genetic effects (A), common environment (C) and unique environment for each twin (E). The model was fitted separately to the abundances of taxa found in more than 2 samples in each arm (*abundance* ~ 1) and used to extract broad-sense heritability.

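### The microbiome arm comparisons in SAP 7.2.2.1 are specified without the twin pair or the baseline sample, so run as written they are conservative and can lose power

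*Combined protocol and SAP*

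**What the plan says.** **Design.** The SAP's randomisation section states: "They will be randomised as twin pairs, with one twin in each arm". SAP 7.2.2.1 states: "Stool samples will be collected from all participants at the beginning and end of the study".

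**Microbiome arm comparisons (SAP 7.2.2.1).** There are two tiers of model. The first is "crude models assessing just the variable of interest (prebiotic supplementation"; the second is "models adjusted for key biological (age, sex, exercise etc.) and technical covariates", with library size as the technical example. For diversity: "Differences in species diversity and richness will be compared between each study arm in regression analysis in crude and adjusted models". For composition: "permutational multivariate analysis of variance (PERMANOVA) will be used to understand differences in composition between each study arm". Protocol 17.2 has essentially the same plan.

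**Other secondary outcomes.** The primary model in SAP 7.2.1 has the pair identifier and zygosity as random effects and baseline chair-rise time as a covariate. Under SAP 7.2.2, grip strength, SPPB, IPAQ, frailty index, cognition and SNAQ "will be analysed using the same method as for the primary outcome, including usage of the baseline value". Serum metabolites also get the 7.2.1 model with their baseline level. Gut microbiome measures are referred on to 7.2.2.1 instead.

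**Supplementary Note 1, section 1.1.1.8.** It reports that "permutational multivariate analysis of variance (PERMANOVA) tests were performed using the `adonis2` function from the `vegan` R package with 1000 permutations", testing marginal effects. It states no restriction on the permutations and does not list the model terms.

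**The concern.** A permutation test should shuffle labels the way the trial assigned them. Here each pair has one twin in each arm, so the only re-assignments the design allows are swaps within a pair. Shuffling freely across all participants, with arm as the only term, leaves the variation between pairs in the null distribution. If co-twins resemble each other, that distribution is too wide and the test rejects too rarely. A diversity regression with arm alone has the same fault, and it also leaves out the participant's own baseline value.

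A microbiome shift is the mechanism the trial proposes, and Specific Aim 2 concerns the links from supplement to microbiome to muscle. A missed shift would be read as evidence against that mechanism. The error is towards false negatives and does not create false positives.

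**Working it through.** **The plan's own figure.** The only power calculation is for chair-rise time. A 20% reduction is log10(1/0.8) = 0.0969. With SD 0.126 this is 0.0969/0.126 = 0.769 SD. At two-sided 5% and 80% power, n = 2(1.960 + 0.842)²/0.769² ≈ 27 per group, or 28 with the t distribution. The plan states 30, which is slightly conservative. That calculation treats the arms as independent samples and says nothing about the microbiome.

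**Inputs.** n = 36 pairs (Supplementary Table S6 has 36 per arm). The within-pair correlation ρ, the baseline-to-end correlation r and the effect size are **assumptions**, shown over ranges.

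**Size of an unpaired test.** The test takes the variance of the arm difference as 2σ²/n, but under pairing it is 2σ²(1−ρ)/n. The effective critical value is therefore 1.96/√(1−ρ):

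| ρ | critical value | true size at nominal 5% |
|---|---|---|
| 0.20 | 2.19 | 2.8% |
| 0.35 | 2.43 | 1.5% |
| 0.50 | 2.77 | 0.6% |

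**Power for diversity.** A paired, baseline-adjusted analysis has variance 2σ²(1−ρ)(1−r²)/n. The table gives power for an end-of-study comparison ignoring pairs → pair plus baseline, with the relative loss from unrounded values:

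| Effect | ρ 0.20, r 0.3 | ρ 0.35, r 0.5 | ρ 0.50, r 0.7 |
|---|---|---|---|
| 0.66 SD | 83→89% (7%) | 85→97% (13%) | 88→~100% (12%) |
| 0.50 SD | 57→68% (15%) | 58→84% (31%) | 59→98% (40%) |
| 0.30 SD | 22→31% (28%) | 20→43% (54%) | 17→69% (76%) |

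The unpaired column uses a normal approximation. Simulating the pooled two-sample test gave powers up to 2 points lower, so these losses are if anything slightly low.

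**PERMANOVA, Bray–Curtis, simulated.** 60 taxa, 199 permutations, 300 runs per setting (Monte Carlo standard error up to √(0.25/300) ≈ 3 points). Free permutation with arm as the only term → permutation within pairs:

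| ρ | size | weaker effect (loss) | stronger effect (loss) |
|---|---|---|---|
| 0.10 | 2.3→4.0% | 33→44% (25%) | 77→83% (7%) |
| 0.20 | 1.3→4.0% | 26→46% (44%) | 74→90% (18%) |
| 0.35 | 0.7→5.7% | 15→53% (71%) | 68→90% (24%) |
| 0.50 | 0→2.7% | 10→66% (85%) | 62→98% (36%) |

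**PERMANOVA, Euclidean, simulated.** 30 features, five of them shifted. At ρ = 0.15, 0.30 and 0.50, the size of the free test is 0.4%, 0% and 0%, against 4–5% within pairs. With a 0.4 SD shift, power is 38 vs 60%, 14 vs 67% and 4 vs 86%; the last is a relative loss of 1 − 4/86 = 95%. With a 0.6 SD shift it is 89 vs 97%, 81 vs 99% and 57 vs 100%.

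**Baseline in PERMANOVA.** A distance test on change scores had less power than within-pair permutation of the end samples (15% vs 44% at ρ 0.1, r 0.5, weaker effect). It used a different distance, so this is indicative only. No gain from baseline is shown for PERMANOVA.

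**The case against.** A reader might infer that the plan ignores the pairing and the baseline altogether. The documents do not support that. SAP 7.2.2 opens with mixed-effects models of change for a list that includes gut microbiome measures. Protocol 10.1, Stage 6, plans repeated-measures mixed models of change. SAP 7.2.2.1 mentions differences between twin pairs, and paired tests. Supplementary Figures S8 to S10 adjust for twin pair, and S9 also for baseline abundance. The PERMANOVA terms are not listed, so a pair term is not ruled out. That matters: in the Euclidean setting with a 0.4 SD shift, fitting pair as a term with permutation left unrestricted gave 56%, 64% and 90% power, against 54%, 64% and 89% for within-pair permutation.

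This removes the charge that the design was disregarded. It does not close the gap. PERMANOVA is not a mixed model, so the general sentences do not say how its permutations respect pairs. A crude model with only the supplement variable contains neither pair nor baseline. The paired tests in 7.2.2.1 relate dissimilarity to muscle strength within each arm, and the supplementary figures are correlations; neither is the randomised contrast.

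It is also fair that these are secondary outcomes and that the error is conservative.

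**Conclusion.** The point holds as a specification gap with a free remedy. SAP 7.2.2.1 states a method for the microbiome arm comparisons that omits the randomised pair and the baseline value, while the same SAP uses both for its other secondary outcomes.

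If arm is the only term and permutation is unrestricted, the tests fall below their nominal 5% whenever co-twins are positively correlated. The relative power loss runs from under 10% (larger effects, or low correlations) to about 85% in the Bray–Curtis runs, and 95% in the most extreme Euclidean setting.

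A reader might infer that most of the power is lost. That is not established. It needs a small effect together with moderate to high correlations, and the documents give no microbiome effect size, within-pair correlation or baseline correlation. The case for using baseline rests on the univariate outcomes only.

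**What to change.** Amend SAP 7.2.2.1 as follows.

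- **PERMANOVA and dbRDA of end-of-study samples:** include twin pair (fid) as a term and permute arm labels only within pairs. List the model terms.
- **Alpha diversity, functional modules and taxa:** model the end-of-study value on arm, the baseline value and a random intercept for pair, in line with 7.2.1. Make this the base model, and let the adjusted tier add age, sex, exercise and library size.
- **Incomplete pairs:** say how they are handled. A pair with one end sample adds nothing to a within-pair permutation but can stay in the mixed model.

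The cost is SAP wording and a few lines of code. No new data are needed, and the coded arm labels suffice, so the blinded analysis is unaffected. Any arm comparison already run without pair or baseline can be rerun on the existing samples.
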